### 2.4. Sample Size

There has yet to be any investigation examining the efficacy of Montmorency tart cherry in patients with UC. Therefore, a pragmatic a priori sample size calculation was undertaken based on a previous trial examining the effects of bilberry supplementation on UC health-related quality of life change scores quantified using the Short Inflammatory Bowel Disease Questionnaire [14]. Considering an expected attrition rate of 20%, this revealed that 20 participants would be necessary in each trial arm, with a total N of 40, to achieve *α* = 5% and *β* = 0.80, enabling an increase in health-related quality of life of 6.5 points to be detected.

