### 3.2. Data Collection

All measurements will be made inside the Physiology laboratory at the University of Hertfordshire and will be carried out in the exact same way on two occasions: at baseline and after six weeks.

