### 3.4. Statistical Analysis

Continuous experimental variables will be presented as mean values along with their corresponding standard deviations. To compare participant characteristics at baseline, as well as compliance levels, experimental anthocyanin intake, experimental energy intake, and experimental sugars (g/day) between the trial arms, between-group linear mixed effects models will be utilized. In these models, the group will be treated as a fixed factor, and random intercepts will be included for participants.

All analyses of the intervention-based data will follow an intention-to-treat approach. To determine the effects of the intervention on all of the outcome measures, differences in the changes from baseline to 6 weeks between the two trial arms will be examined using linear mixed-effects models with a group modelled as a fixed factor and random intercepts by participants adopted. For linear mixed models, the mean difference between groups in changes from baseline to 6 weeks (*b*) and 95% confidence intervals of the difference will be presented. Effect sizes were calculated for the changes from baseline to 6 weeks between the two groups, using Cohen’s *d*, in accordance with McGough & Faraone [51]. Cohen’s d values will be interpreted as 0.2 = small, 0.5 = medium, and 0.8 = large [52]. The efficacy of blinding will be assessed using a one-way chi-square (*Χ*^2^) goodness-of-fit test. Chi-square analyses will be calculated using Monte-Carlo simulation to determine probability values. All statistical analyses will be performed using SPSS v28 (IBM Inc., SPSS, Chicago, IL, USA), and statistical significance will be considered at a *p* ≤ 0.05 level.

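### The mixed model in section 3.4 is fitted to one change score per participant, so it reduces to an unadjusted change-score comparison and does not by itself deliver the stated intention-to-treat analysis

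*Protocol article*

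**What the plan says.** Section 3.4 of the protocol article states that "All analyses of the intervention-based data will follow an intention-to-treat approach". For all outcome measures it then says that "differences in the changes from baseline to 6 weeks between the two trial arms will be examined", and that this is done "using linear mixed-effects models with a group modelled as a fixed factor and random intercepts by participants adopted". The reported coefficient b, with its 95% confidence interval, is "the mean difference between groups in changes from baseline to 6 weeks". No visit term, group×visit term or baseline covariate is named.

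Section 3.2 says that measurements "will be carried out in the exact same way on two occasions: at baseline and after six weeks"; section 2.1 gives the same two time points. Section 2.4 plans 20 participants per arm, "Considering an expected attrition rate of 20" per cent.

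The opening paragraph of section 3.4 uses the same construction for baseline characteristics, compliance and experimental intakes: group as a fixed factor, and "random intercepts will be included for participants".

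**The concern.** A participant random intercept separates between-person from within-person variation, which needs more than one row per person. If the outcome is the change between the only two visits, there is one row per person and nothing to separate. Three things are then at stake.

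- **The model is not what its name says.** It can be fitted only with a redundant term, and software may warn, fail or report an unreliable standard error.
- **The intention-to-treat label.** A mixed model on the repeated raw scores would keep a participant who has only a baseline value. A model on change scores cannot.
- **Baseline is not conditioned on.** A plain change-score comparison is less precise than one that conditions on baseline. It is also open to bias if participants who start worse leave one arm more than the other. The primary endpoint is a self-reported questionnaire in a small trial.

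**Working it through.** **Inputs from the protocol article.** Two visits (2.1, 3.2); outcome = change, fixed effect = group, random effect = participant intercept, b = difference in mean change (3.4); 20 per arm, 40 in total, 20% attrition (2.4).

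**1. Numbers analysed.** 20 × (1 − 0.20) = 16 per arm, so 32 of 40 have a change score and 40 × 0.20 = 8 do not.

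**2. Identifiability.** With one row per participant the model is yᵢ = a + b·groupᵢ + uᵢ + eᵢ, with Var(yᵢ) = σ²ᵤ + σ²ₑ and no covariance between rows. Only the sum of the variances enters the likelihood. In one simulated data set of 40 randomised with 8 missing week 6:

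| Random-intercept share of variance | REML log-likelihood | b | SE |
|---|---|---|---|
| 0, 0.10, 0.25, 0.50, 0.75, 0.90, 0.99 (all identical) | −63.0073 | 6.774 | 1.597 |

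The pooled two-sample t-test on the same 32 participants gives the same b and SE (30 df). One general-purpose mixed-model routine (not SPSS) returned an arbitrary 50:50 split (10.20 and 10.20), a warning of a non-positive-definite Hessian, and an SE of 0.714 instead of 1.597.

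**3. Could the text mean raw scores in long format?** With group as the only fixed factor, b would be the group difference averaged over both visits. In the same data this gives 2.27. A long-format model with group×visit gives 6.53 (SE 1.57), using 72 rows from all 40 participants, and its intercept and residual variances are separable (34.3 and 10.1). Only the change-score reading matches both the stated fixed effect and the stated b.

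**4. Precision.** In units of the baseline SD, assuming equal SDs at both visits and correlation ρ, with 16 per arm and random dropout:

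- Change score: SE = √[(2/16) × 2(1 − ρ)].
- Baseline-adjusted: SE ≈ √[(2/16) × (1 − ρ²)], slightly more in small samples.
- Ratio of variances: (1 − ρ²) / [2(1 − ρ)] = (1 + ρ)/2.

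| ρ | Change-score SE (formula) | Adjusted SE (formula) | Variance ratio | Simulated SEs, change v adjusted |
|---|---|---|---|---|
| 0.3 | 0.42 | 0.34 | 0.65 | 0.41 v 0.35 |
| 0.5 | 0.35 | 0.31 | 0.75 | 0.36 v 0.31 |
| 0.7 | 0.27 | 0.25 | 0.85 | 0.27 v 0.26 |

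**5. Bias under assumed dropout, no true effect.** In the extreme case the 4 placebo participants with the lowest baseline leave and 4 active participants leave at random. The expected four lowest of 20 standard normal values are −1.867, −1.408, −1.131 and −0.921, which sum to −5.327. The 16 remaining placebo participants therefore start 5.327/16 = 0.333 SD above the mean. Their expected change is −(1 − ρ) × 0.333, which favours cherry by 0.23, 0.17 and 0.10 SD at ρ = 0.3, 0.5 and 0.7. Simulation agrees to within about 0.01.

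| Dropout pattern | Change-score bias at ρ = 0.3, 0.5, 0.7 | Baseline-adjusted, same 32 completers |
|---|---|---|
| Extreme, as above (simulated) | 0.24, 0.16, 0.10 | about 0 |
| Graded: placebo dropout weight exp(−0.7 × baseline z) | 0.11, 0.08, 0.05 | not tabulated |
| Lowest four leave in both arms, or random in both | about 0 | about 0 |

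**The case against.** The redundant intercept does no harm to the estimate: b is the same under every split of the variance, and a correctly computed SE equals that of the t-test. SPSS v28, the package named in section 3.4, was not run, so the wrong SE from another routine shows only what can happen. This stands.

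A reader might infer that losing 8 of 40 participants is what biases the result. The working does not support that. Baseline-adjusted regression on the same 32 completers removes the bias, so its source is the failure to condition on baseline. It also requires dropout that depends on baseline differently by arm. Section 2.4 gives only an overall attrition rate and nothing that points to differential dropout. Even the extreme bias is below one standard error of the estimate.

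A reader might also infer that the trial cannot be analysed by intention to treat. That goes too far. The article condenses a fuller plan, and imputation before change scores are formed is commonly left to the statistical analysis plan. It would keep the dropouts. It would not make the random intercept estimable in the model as worded.

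The baseline and compliance comparisons have the same redundancy, most naturally with one value per participant, but they are descriptive and do not feed the primary inference.

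**Conclusion.** The point holds in this form: the outcome, fixed effect, random effect and b fixed in section 3.4 do not together make an estimable mixed model. They amount to an unadjusted two-sample comparison of change scores. That conclusion is algebraic and rests on no assumption beyond one change score per participant.

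As worded, the model does not by itself deliver intention-to-treat: about 8 of 40 participants would contribute nothing at the planned attrition, unless a plan not shown imputes. The loss of precision is moderate (adjusted variance 65% to 85% of the change-score variance for correlations 0.3 to 0.7, assuming equal SDs). The bias is conditional: about 0.24 to 0.10 baseline SD in the extreme assumed case, roughly half that under graded dropout, and about 0 if dropout is random or similar in both arms. The documents do not support a claim that b is invalid or that the result will be biased.

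**What to change.** Reword section 3.4 before unblinding:

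- Analyse raw scores at both visits from all randomised participants in one model, with visit and group×visit terms, baseline means constrained equal across arms, and an unstructured 2×2 covariance. For completers, regressing the week-6 score on group and baseline is equivalent.
- Report the week-6 group contrast as b, with its 95% confidence interval.
- Use ordinary linear models or plain summaries where there is one value per participant, such as baseline characteristics and compliance.

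A sensitivity analysis for missing week-6 scores is an optional addition. The cost is a few sentences and slightly more analysis code. No new data, visits or participants are needed, because the baseline scores are already collected.

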### 3.5. Ethical Approval and Registration

This study has been granted ethical approval by the University of Hertfordshire Health, Science, Engineering and Technology Ethics Committee (cLMS/SF/UH/05240), and has formally been registered as a trial (NCT05486507). When the data have been evaluated, participants who request to see a summary of the study results will be given that information. Publication in a peer-reviewed journal and presentation at both national and global scientific conferences will be the primary means of disseminating the study findings from this trial.

### 3.6. Dissemination

The results and conclusions of this study will be communicated to a broad range of local, national, and international audiences as part of its dissemination strategy. We will include someone with UC on the trial steering group and include them within steering meetings. On completion of the trial, we will disseminate the results through local inflammatory bowel disease support groups. To best facilitate user distribution, we will coordinate with our patient representatives and regional authorities on patient and public involvement. We intend to create a specialized information article that will be distributed to the proper organizations. We will produce peer reviewed publications and present at an international conference.

### 3.7. Safety Reporting

The Sponsor’s Adverse Event Reporting Procedures shall be followed for reporting adverse events. The clinical co-investigator will be in charge of assessing the cause and severity of adverse events, as well as ensuring that appropriate action is done. Data on adverse events will be gathered from the start of any study-related procedure (i.e., upon acquisition of written consent). The participant’s final trial contact will mark the end of the adverse event reporting period.

Throughout the study, we will closely monitor and document both significant and non-serious adverse effects that may be associated with participation in the research or lead to withdrawal from the or study. Serious adverse events encompass any unfavorable medical event. In the event of any necessary modifications to the experimental protocol, we will promptly inform the study ethics committee for reevaluation and approval, and the trial registry will be updated accordingly. During this period, data collection will be temporarily halted. Non-serious incidents, on the other hand, encompass medical occurrences that do not meet the criteria for serious adverse events.

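### The safety section gives two inconsistent scopes for recording adverse events, and its definition of serious leaves the non-serious class empty

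*Protocol article*

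**What the plan says.** All the relevant text is in section 3.7 (Safety Reporting) of the Protocol article.

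The first paragraph names the governing procedure: "The Sponsor’s Adverse Event Reporting Procedures shall be followed for reporting adverse events". It assigns assessment: "The clinical co-investigator will be in charge of assessing the cause and severity of adverse events". It then sets the period. At the start, "Data on adverse events will be gathered from the start of any study-related procedure", which the article equates with written consent. At the end, "The participant’s final trial contact will mark the end of the adverse event reporting period". Relatedness is not mentioned as a condition for gathering the data.

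The second paragraph describes what will be done during the study: "we will closely monitor and document both significant and non-serious adverse effects". The sentence goes on to qualify these as "adverse effects that may be associated with participation in the research or lead to withdrawal" from the study.

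On seriousness, the same paragraph states "Serious adverse events encompass any unfavorable medical event". It closes by defining non-serious incidents as medical occurrences that fail the criteria for a serious event.

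**The concern.** The two paragraphs can lead a site to keep two different event logs. Under the first, an event is gathered and its cause is assessed afterwards. Under the second, a view on possible cause comes before documentation.

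This matters in the trial's population. Section 2.2 enrols people with mild to moderate active ulcerative colitis, so a worsening during the six weeks is easily put down to the disease. The two drinks also differ in composition. Per 30 mL, section 3.1.1 gives 15 g of sugars and 1 g of fibre for the cherry concentrate, and section 3.1.2 gives 20 g of maltodextrin with no sugars or fibre for the placebo. If either drink affects symptoms, attributing events one by one is a weak way to find out. Comparing the randomised arms is a better way, but only if events are recorded whatever their presumed cause.

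The definition of serious raises a separate problem. If every unfavourable medical event is serious, the label carries no information, and the article's own separate treatment of serious and non-serious events cannot be applied.

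**Working it through.** The point rests on no figure in the article, so the check is of the text.

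**Step 1: compare the two scopes.** The clause in the second paragraph is restrictive: it says which effects are monitored and documented. Classify events by the two conditions it names and read each paragraph literally.

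| Event | First paragraph | Second paragraph |
|---|---|---|
| Possibly associated with participation, leads to withdrawal | gathered | documented |
| Possibly associated, participant continues | gathered | documented |
| Not thought associated, leads to withdrawal | gathered | documented |
| Not thought associated, participant continues | gathered | not covered |

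The paragraphs agree on three rows. They differ on the fourth, which is where a flare put down to the underlying disease would fall if the participant stays in the trial.

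**Step 2: check the order of assessment.** The first paragraph has the clinical co-investigator assess the cause of adverse events in general. That is an assessment of events already captured, and it fits poorly with possible association being a condition of capture.

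**Step 3: check the definitions.** Let U be all unfavourable medical events. The article sets serious = U. It sets non-serious = events in U that are not serious. So non-serious = U minus U, which is empty. The severity assessment in the first paragraph does not repair this, because severity and seriousness are different attributes.

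**Step 4: look for an analysis that would be affected.** Sections 1.2 and 2.1 list quality of life, other questionnaires and biological indices, with no safety objective or outcome. Section 3.4 compares arms on the outcome measures and describes no comparison of adverse events. Any effect on a comparison of harms is therefore a consequence for later use of the data, not damage to a stated analysis.

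**Step 5: look for a size.** The article gives no expected adverse-event rate and no basis for the share of events in the fourth row. A computed loss of precision or power would reflect only the values assumed for these, so none is given.

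**The case against.** The strongest case on the other side has four parts.

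- **A period and a scope can coexist.** The first paragraph fixes when data are gathered and the second fixes what is closely followed. A reader might infer that only events judged to be related are recorded. The article does not use those words, and it does not say that other events go unrecorded. Nor does the first paragraph say that all events are collected. This stands: the fault is an inconsistency to be reconciled, not an announced decision to discard events.
- **The threshold is low.** Possible association with taking part in the research is a wide net, and worsening that leads to withdrawal is expressly covered. In a placebo-controlled trial the filter might fall about equally on both arms. This limits the likely loss, but the article does not settle it.
- **Worsening is measured elsewhere.** The SCCAI and the quality-of-life questionnaire (section 3.2.1) and faecal calprotectin (section 3.2.2) are collected in both arms whatever the attribution, and are compared by intention to treat. A reader might infer that a worsening caused by a drink would go unseen; these measures largely answer that for the state at week 6. They do not answer it for a transient flare, because section 3.2 provides for measurement only at baseline and after six weeks.
- **The Sponsor's procedures govern and are not shown.** They may settle both the scope and the meaning of serious. If so, the article misdescribes them and should be brought into line. This is not a case of an article leaving detail to a fuller document, since it states a scope and a definition and both are faulty as worded.

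A reader might also infer that a planned safety comparison is compromised, or that the trial is justified by fewer side effects. Neither is supported. No such comparison is stated, and fewer side effects appears as background in the Abstract and Introduction, while section 1.1 rests on the absence of trials and on patients' willingness.

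**Conclusion.** The point holds as two wording faults in one section.

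First, the scope of recording differs between the two paragraphs for events that are not thought associated with participation and do not lead to withdrawal. Followed literally, the second paragraph would leave those events undocumented and would filter any later comparison of harms. This rests on reading the qualifying clause as restrictive, which is its plain sense, and on the Sponsor's procedures not overriding it, which cannot be checked here.

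Second, the definition of serious empties the non-serious class. This needs no inference beyond the two sentences themselves.

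Neither fault touches the primary outcome or its analysis. The size of the first cannot be estimated from the article. Correction is worthwhile because it is cheap, and because events left undocumented during the trial cannot be reliably recovered later.

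**What to change.** Reconcile the two paragraphs of section 3.7. State once that every adverse event from written consent to the final trial contact is recorded regardless of attribution, and remove possible association and withdrawal as conditions of documentation. Keep relatedness as a separate assessment of recorded events, in line with the role already given to the clinical co-investigator. Replace the sentence defining serious events with the definition in the Sponsor's procedures, so that the non-serious class is again distinct.

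The cost is a few sentences of text and a slightly longer event log, with no added visits or measurements. The change should be made before events are collected. Section 3.7 sends protocol modifications to the ethics committee and the registry and pauses data collection meanwhile, so a later change could carry that additional cost.

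### The safety section defines a serious adverse event so broadly that no adverse event can be non-serious, although it plans to document both classes

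*Protocol article*

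**What the plan says.** Everything relevant stands in section 3.7 (Safety Reporting) of the protocol article.

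- The governing procedure: "The Sponsor’s Adverse Event Reporting Procedures shall be followed for reporting adverse events".
- Who assesses events, and for what: "The clinical co-investigator will be in charge of assessing the cause and severity of adverse events". The same role must also see that suitable action is taken.
- What will be recorded: "we will closely monitor and document both significant and non-serious adverse effects". The sentence goes on to limit these to effects that may be linked to taking part or that lead to withdrawal.
- The serious class: "Serious adverse events encompass any unfavorable medical event". The sentence ends there.
- The non-serious class, at the end of the same paragraph: "Non-serious incidents, on the other hand, encompass medical occurrences that do not meet the criteria for serious adverse events".

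No other section of the article defines seriousness or returns to the subject.

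**The concern.** A definition of a serious event has to pick out a subset of adverse events. This one does not: its wording fits an adverse event of any kind. The second definition depends wholly on the first, because it describes the non-serious class only as what remains, and it points to criteria that the article never states.

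What is at stake is the meaning of the label. Participants have active ulcerative colitis of mild to moderate degree (section 2.2), and adverse events are collected from consent until the last trial contact (section 3.7). If staff applied the article's rule, a brief, minor complaint and a grave event would carry the same label. Any number of serious events reported later would then be just the number of adverse events. A reader of the results could not tell from the article what that number means.

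**Working it through.** No figure is at issue, so there is nothing to calculate. The check sets the sentences of section 3.7 side by side.

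1. Let A be the set of all adverse events, that is, all unfavourable medical events in participants. Let S be the serious class and N the non-serious class.
2. From "Serious adverse events encompass any unfavorable medical event": any member of A belongs to S, so A is contained in S.
3. From the words that non-serious incidents "encompass medical occurrences that do not meet the criteria for serious adverse events": N is the complement of S.
4. Steps 2 and 3 together: an adverse event lies in A, hence in S, hence not in N. The overlap of A and N is empty.
5. From "we will closely monitor and document both significant and non-serious adverse effects": two kinds of adverse effect are meant to be recorded, one of them non-serious. This needs the overlap of A and N not to be empty, which contradicts step 4. The step takes 'significant' as the counterpart of 'non-serious', that is, as 'serious'. If 'significant' means something else, the contradiction remains, because non-serious adverse effects are still expected to exist.

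Two looser readings were tried.

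- If 'encompass' means 'include' and not 'consist of', S may hold more than A, but it still holds all of A. Step 4 is unchanged.
- If 'medical occurrences' is wider than unfavourable events, N may hold occurrences that are not unfavourable. Those are not adverse events, so N is still empty of adverse events.

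A last check was whether the section supplies a criterion by another route. The sponsor's procedures are invoked for the reporting of adverse events, and the article does not say that they supply the definition of seriousness. The clinical co-investigator is to assess cause and severity. Severity is the intensity of an event and is not the same as seriousness, which is not named among the assessments.

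**The case against.** The strongest reply is that this is a careless or cut-off sentence in a condensed article and not a rule that anyone will follow. The section opens by placing reporting under the sponsor's procedures. Its last sentence refers to criteria as though they exist, and it plainly intends two classes. An article need not reproduce the full list of criteria. Much of this stands. The procedures are not shown and may contain proper criteria, so actual classification may be correct. The absence of a list is not the complaint. The complaint is that the article does give a definition, and that definition defeats the split made in the same paragraph. If the procedures hold sound criteria, the article conflicts with them.

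A reader might also infer more than the text supports:

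- **That serious events would be missed or not acted on.** A definition that is too wide over-reports and does not by itself let an event escape. The clinical co-investigator is also charged with ensuring suitable action.
- **That a between-arm safety analysis is spoiled.** The article plans none. Safety is not named among the outcomes in sections 1.2, 2.1 and 3.2, and section 3.4 does not mention adverse events.
- **That every adverse event would halt data collection.** The temporary halt follows a sentence about modifying the protocol and is not clearly tied to the occurrence of a serious event.

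**Conclusion.** The point holds as an error in the text. As written, section 3.7 puts every adverse event in the serious class and leaves no adverse event in the non-serious class, against its own plan to document both. A count of serious events made under that wording would carry no information on seriousness.

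The all-or-none result follows from the wording and does not forecast how staff will classify events. It rests on reading the article alone, with the sponsor's procedures unseen. The error does not touch the primary outcome, the sample size or any analysis that the article states. It deserves correction because a stated rule gives the wrong classification when followed, and because putting it right costs very little.

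**What to change.** Reconcile section 3.7 with the sponsor's procedures that it already cites. Keep the present wording, but attach it to the term 'adverse event'. Define a serious adverse event by the criteria in those procedures, either quoted or by explicit reference, so that the later mention of criteria has something to point to. The definition of non-serious incidents can then stand as it is. Using 'serious' in place of 'significant' in the sentence on documentation would make the two classes match.

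Which criteria apply is for the sponsor's procedures to say, and none is proposed here. The cost is about one sentence of text, with no change to design, sample size, outcomes or analysis.
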